## Abstract

**Background:**

CARA set out to develop a data-visualisation platform to facilitate general practitioners to develop a deeper understanding of their patient population, disease management and prescribing through dashboards. To support the continued use and sustainability of the CARA dashboards, dashboard performance and user engagement have to be optimised. User research places people at the centre of the design process and aims to evaluate the needs, behaviours and attitudes of users to inform the design, development and impact of a product.

**Objective:**

To explore how different initial key messages impact the level of behavioural engagement with a CARA dashboard.

**Methods:**

Participating general practices can upload their practice data for analysis and visualisation in CARA dashboards. Practices will be randomised to one of three different initial landing pages: the full dashboard or one of two key messages: a between comparison (their practice prescribing with the average of all other practices) or within comparison (with practice data of the same month the previous year) with subsequent continuation to the full dashboard. Analysis will determine which of the three landing pages encourages user interaction, as measured by the number of ‘clicks’, ‘viewings’ and ‘sessions’. Dashboard usage data will be collected through Google analytics.

**Discussion:**

This study will provide evidence of behavioural engagement and its metrics during the implementation of the CARA dashboards to optimise and sustain interaction.

**Trial registration:**

ISRCTN32783644 (Registration date: 02/01/2024).

## Background

Most general practices have computerised patient management systems (PMS). However, few PMS provide options to perform data reporting and exploration, audit and feedback, in-depth analysis of aggregated patient data or comparison and benchmarking with other general practices [1, 2]. The use of dashboards and data visualisations is growing in the health sector, in particular since the pandemic, when numerous exemplars were designed to allow fast and easy comparisons [3, 4]. However, these visual analytics processes imply access and integration of data [5] and challenges remain as data is recorded through different, often incompatible systems (data silos) for which project specific, bespoke dashboards are designed [4, 6].

Dashboards are generally launched for one sole purpose, such as research, exploratory, analytical or business. Dashboard are on the whole, designed ‘for’ and not ‘with’ users and allow limited, if any, user interaction or engagement [3, 7, 8]. Once set up, dashboards require continuous input from the developers to maintain their relevance [3], which must be tailored to the end users’ needs. Developers should employ iterative evaluation of dashboard performance during the development and implementation to promote uptake and use of the dashboard [9]. Researchers and developers have to maintain the effectiveness and relevance of the dashboard in terms of health outcomes and user engagement.

User engagement is a complex concept that incorporates emotional, cognitive and behavioural dimensions [10]. Emotional engagement entails the processing of visual, tactile, auditory and interactive cues by the user’s attentional faculties. Cognitive engagement pertains to problem-solving and sensory aspects of the experience, encompassing enjoyment, boredom, curiosity, stimulation of imagination and evoked interest. Behavioural engagement is linked to interactivity and serves as a key element in enhancing the sensory dimension of the experience [10]. Behavioural engagement revolves around the user’s interactions with the product and their responses to its feedback. It includes the frequency and extent of user interactions, along with the time needed to accomplish tasks or engage with content. Interaction serves as a tangible representation of a user’s behavioural engagement with the product, signifying active user participation during these stages. The metrics employed typically involve tracking the number of clicks, pages visited, video durations watched and views of specific content pages [10].

User research combines qualitative and quantitative research methods to evaluate the needs, behaviours and attitudes of users to inform the design, development and impact of a product [11]. For the evaluation of a data dashboard, a process evaluation involves understanding how users interaction with the dashboard (i.e., clicks, views and duration on the interaction), which helps inform the dashboard’s adaptation to maximise user exposure [12]. Monitoring web traffic sources through Google Analytics provides quantitative data on dashboard usage [12, 13] and allows measuring user perceptions or behaviour indirectly [12, 14–16]. Furthermore, these web traffic sources allow developers to estimate and infer the level of behavioural engagement on website platforms. Overall, a strong level of behavioural engagement groups several indicators from Google Analytics, such as high returning users numbers, low bounce rate, high page viewed numbers per session, high mean session duration and lofty goal conversion rates [12, 16, 17].

The CARA project is designed as a sustainable data-sharing platform that can be applied across different PMS to facilitate general practitioners to develop a deeper understanding of their patient population, disease management and prescribing through dashboards [18, 19]. The CARA infrastructure consists of a common data model (to combine data from different PMS), CARAconnect to upload data and CARA dashboards for visualising data. The first exemplar dashboard is focused on antibiotic prescribing and includes automated audit reports, filters (within practice) and between-practice comparisons [18, 19]. The antibiotic Anatomical Therapeutic Chemical code J01 was used for this antibiotic dashboard and categorised into green (preferred – antibiotics are more effective, have fewer side effects and are less likely to lead to resistant infections) and red (non-preferred - antibiotics should not be used in primary care unless absolutely necessary) antibiotics according to Irish national guidelines [20, 21].

To design the CARA dashboard, action design research (ADR) was used, which generates knowledge about how to solve organisational problems in practice. ADR includes four steps (a) problem formulation, (b) building, intervention and evaluation, (c) reflection and learning and (d) formalisation of learning [22, 23]. During the development and testing of the CARA dashboard, it became clear that dashboard performance (i.e. behavioural engagement and interaction) is important for continued use and sustainability of the dashboard. Hence, it is essential to implement user research to quantify how users (practices) interact with the dashboards and how to influence user behaviour. Previous research showed that behavioural interventions based on peer comparison can have a marked effect on the prescribing decisions of health professionals [24–26]. This study will implement user research to explore how different initial key messages impact the level of behavioural engagement with the CARA dashboard.

## Method

### Study design

General practices will be randomised to one of three different initial landing pages (groups): the full dashboard or one of two key messages. All practices have access to the same dashboards and view identical information but two groups will be shown a key message before they can continue to the full CARA dashboard [27]. The key messages are similar and focus on one of the charts from the existing dashboard (Figs. 1 and 2):

**Fig. 1 Fig1:**
[figure not shown]
Details of the three different initial landing pages (groups)

**Fig. 2 Fig2:**
[figure not shown]
Overview of the allocation of practices to group A, B or C

### Participants

General practices that register with the CARA network for access to the dashboards will be randomised (practice level) using a computer-generated system, which will allocate to either group A, B or C using 1:1:1 randomisation (Fig. 1). Practices are NOT allocated to different dashboards but to different initial landing pages from where they can access the full dashboard.

### Recruitment

General practices will be invited to join the CARA network [18] through social media and direct mailing through the Irish College of General Practitioners. Registration with the CARA network [18] is open to all general practices. Once registered and after confirming terms and conditions, the general practice receives a link to CARAconnect (to de-identify, extract and upload data) and view their practice data in the CARA dashboards.

### Outcomes

The primary outcome is behavioural engagement (measured as the number of ‘clicks’, ‘viewings’ and ‘sessions’) with the CARA dashboard after one month of dashboard usage collected through Google Analytics (Table 1).

**Table 1 Tab1:** Terminology definition of behavioural engagement outcomes (from Google Analytics [28])

Outcomes	Definition
Conversion event	Every ‘click’ on the antibiotic dashboard page (clicks include filters, comparisons with other practices and audit)
Session Conversion rate	The number of conversion events (at least one) divided by the total number of sessions*
Engaged sessions	The number of sessions* that lasted at least 10 s, had 1 or more conversion events or 2 or more page or screen views
Engagement rate	The number of engaged sessions divided by the total number of sessions*
Bounce rate	The number of sessions that were not engaged divided by the total number of sessions*
Average session duration	The average duration (in seconds) of users’ sessions*.

* A session initiates when a user opens the CARA dashboard. By default, a session ends or times out after 30 min of user inactivity

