### Data collection

This study will run for a limited time, dashboard usage data will be collected for each practice for a month from the time of enrolment. All practices registering with the CARA network will be included in the randomisation. Dashboard usage data will be collected through Google analytics, which is an integrated part of CARA. Google Analytics provides anonymous data on the behavioural engagement with a page irrespective of who is engaging. Therefore, three identical websites (dashboards) will be set up, two of which will contain an additional landing page with a key message. At no stage IP addresses will be recorded or tracked. Table 1 shows the behavioural engagement data that will be collected.

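### As Table 1 is written, the extra landing page itself counts towards engaged sessions and probably viewings, which favours both key-message groups over the full-dashboard group if most users continue

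*Protocol article*

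**What the plan says.** The Outcomes section of the protocol article defines the primary outcome as behavioural engagement, "measured as the number of ‘clicks’, ‘viewings’ and ‘sessions", over one month. Table 1 then defines the measures. A session is engaged if it meets any one of three criteria: it lasted at least 10 seconds, or it "had 1 or more conversion events or 2 or more page or screen views". The engagement rate is "The number of engaged sessions divided by the total number of sessions" and the bounce rate is "The number of sessions that were not engaged divided by the total number of sessions". A conversion event is a click on the antibiotic dashboard page. The footnote to Table 1 adds: "A session initiates when a user opens the CARA dashboard".

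Under Study design, "two groups will be shown a key message before they can continue to the full CARA dashboard". Under Data collection, "three identical websites (dashboards) will be set up, two of which will contain an additional landing page with a key message". Nothing in the article removes the message page from page views, from session time or from the engaged-session criteria.

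**The concern.** The randomised difference between the groups is an extra page, and one way to be scored as engaged is to have seen two pages. The intervention can therefore satisfy the outcome criterion by itself. A user who opens the site, passes the message and leaves the dashboard at once is engaged in a key-message group. The same conduct on the dashboard is a bounce in the full-dashboard group.

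The study asks which landing page encourages interaction. On the affected measures, a comparison of either message with the full dashboard would mix any real effect with a difference in how the groups are scored. Randomisation does not remove this, and more sessions only make the artefact more likely to reach significance.

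**Working it through.** The article gives no engagement rate, so there is no figure of its own to reproduce on this point. Its only planning mean (23.6 clicks, SD 14.8) concerns clicks, which this mechanism does not touch.

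**Step 1: the same behaviour under the rule.** The user reaches the dashboard, does nothing and leaves, with under 10 seconds in total.

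| Group | Page views | Dashboard clicks | Scored as |
|---|---|---|---|
| Full dashboard | 1 | 0 | not engaged (bounce) |
| Either key message | 2 | 0 | engaged |

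**Step 2: which measures move.**
- Engaged sessions, engagement rate and bounce rate move directly through the two-view criterion.
- Viewings gain one per continuing session. The term is not defined in Table 1, so this assumes that the landing page is counted.
- Average session duration includes the time on the landing page. That time also runs towards the 10-second criterion.
- Conversion events do not move, because they must occur on the antibiotic dashboard page. The session conversion rate and the session count do not move either.
- The contrast between the two messages is largely unaffected, because both groups have the extra page.

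**Step 3: size for the engagement rate.** Let e be the share of sessions that would be engaged on dashboard behaviour alone, and c the share of otherwise non-engaged sessions that continue past the message. Both are assumptions. With identical dashboard behaviour in all groups:

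- full-dashboard group: e
- key-message groups: e + (1 − e)c
- artefact: (1 − e)c

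The last column below is the chance of a significant two-sided result at 0.05 from the artefact alone. It uses a normal approximation with 29 independent sessions per group, that is, one per practice at the planned size. With d the artefact and p̄ the mean of the two rates, it is Φ[(d − 1.96·SE0)/SE1], where SE0 = √(p̄(1 − p̄)·2/29) and SE1 = √((p1(1 − p1) + p2(1 − p2))/29).

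Example, e = 0.7 and c = 0.8: p2 = 0.7 + 0.3 × 0.8 = 0.94, d = 0.24 and p̄ = 0.82. Then SE0 = 0.101 and SE1 = 0.096, so (0.24 − 0.198)/0.096 ≈ 0.44 and Φ ≈ 0.67.

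| e | c | Key-message rate | Artefact (points) | Chance of significance |
|---|---|---|---|---|
| 0.5 | 0.8 | 0.90 | +40 | 0.94 |
| 0.5 | 0.9 | 0.95 | +45 | 0.99 |
| 0.7 | 0.8 | 0.94 | +24 | 0.67 |
| 0.7 | 0.9 | 0.97 | +27 | 0.81 |
| 0.9 | 0.8 | 0.98 | +8 | 0.25 |
| 0.9 | 0.9 | 0.99 | +9 | 0.32 |

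The nominal rate is 0.05. The approximation is rough in the last two rows, where few sessions are non-engaged. If c = 1, the message groups score 100% engaged and 0% bounce whatever e is.

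**Step 4: a harsher assumption.** Suppose that everyone who leaves at the message counts as not engaged, including people who would have been engaged on the dashboard. With C the overall continuation rate, the difference is C − e:
- e = 0.6, C = 0.80 to 0.95: +20 to +35 points
- e = 0.8, C = 0.90 to 0.95: +10 to +15 points
- e = 0.95, C = 0.90: −5 points

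So the direction depends on most users continuing.

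**Step 5: with the message-page view and time not counted,** the Step 3 model gives e in all three groups and an artefact of zero.

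**The case against.** Five points can be made on the other side.

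*The outcome that sizes the study is safe.* Sample size rests on conversion events, and a click to continue from the message page is not a click on the antibiotic dashboard page. This stands, and it limits the point.

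*Baseline engagement may be high.* Users are practices that registered and uploaded their own data, and the planning mean is 23.6 clicks. That mean comes from a usability test and is not a per-session figure, so it is only indicative. Still, with e near 1 the effect on engagement and bounce rates is small. This stands as a limit on size.

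*The footnote may start the session only when the full dashboard opens.* Data collection treats website and dashboard as the same thing and places the landing page inside two of the websites, so the plain reading includes the message page. On the other reading, people who leave at the message disappear from the denominator in two groups only. A reader might infer that this biases results the same way. For rates it could. For the primary counts it does not, because sessions and viewings would fall in the message groups. The wording should be clarified, but no single direction follows.

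*A page filter may sit in the full protocol or analysis plan.* It may. But the point does not rest on missing detail: the definition is stated, and as stated it scores the groups differently.

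*Excluding landing-page time may handicap the messages.* Study design says that each message focuses on a chart that is also on the dashboard. A full-dashboard user's time on that chart counts, while a message user's time on the same content would not. This stands. It makes the treatment of time more debatable than that of the page view, and the fix allows for it.

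**Conclusion.** The point holds in a limited form. Table 1 lets the extra landing page meet the two-view criterion, so merely continuing counts as engagement in two groups and not in the third. If most users continue, this favours the message groups over the full-dashboard group on engaged sessions, engagement rate and bounce rate. It lengthens session duration and, if the landing page is counted, raises viewings, which is one of the three named primary measures.

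Over the assumed ranges in Step 3, the artefact in the engagement rate runs from +8 to +45 points. These figures are illustrations: the article gives neither the baseline nor the continuation rate, nor the number of sessions per practice, and sessions were treated as independent.

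A reader might infer that the message groups must look better on every outcome, or that any significant result would be an artefact. The article does not support that. Clicks, session conversion rate and the session count are not inflated by this route, the contrast between the two messages is largely free of it, and the direction for the rates can reverse if many users leave at the message.

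**What to change.** Amend Table 1 before the data are analysed:

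1. State that the landing-page view and the click to continue do not count towards viewings or the engaged-session criteria in any group.
2. Keep every session that opened the assigned entry page in the denominator in all three groups, so that leaving at the message counts as not engaged, and reword the session footnote to match.
3. Base the main duration measure and the 10-second criterion on time from loading of the full dashboard. Also report total time including the landing page, because the message shows a chart that is also on the dashboard.
4. Base the comparison of each message with the full dashboard on dashboard-page clicks and these redefined measures.

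The cost is a page filter in the analytics export and a revised table. The default engaged-session metric can no longer be used unmodified.

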### Sample size

Sample size is calculated based on the conversion event (number of clicks on the interaction with the antibiotic dashboard page, see Table 1) using a comparative usability test to determine differences between group A, B and C (between-group design) [29, 30]. A comparative usability test is a method for describing and comparing the usability of more than one application [29, 30]. The variance estimation is obtained from a usability test for a similar experiment, which reported the mean number of mouse clicks for dashboard usage (mean = 23.6 and standard deviation = 14.8) [31]. A total sample size of 87 users or practices (29 per group) is estimated to be sufficient to observe a 10% difference [7, 32] with 5% statistical confidence [29, 30].

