### Data analysis

The quantitative information collected will be summarised (descriptive characteristic table) using the mean and standard deviation or, if not normal, with medians and interquartile ranges. Categorical variables will be summarised with counts and proportions. Depending on the data distribution, the continuous measures analysis will use linear regressions or generalised estimating equations for binary and count data. The *N* − 1 two-proportion test (A/B testing) will be used (for small sample sizes) to compare differences in proportions [33]. All statistical tests will be 2-tailed and significance will be set at a p-value of 0,05. Analysis will be performed using R-4.0.3® software.

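### With the plan's own mean and SD, 29 practices per group give about 9% power for a 10% difference in clicks, so the sample size is not sufficient as claimed

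*Protocol article*

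**What the plan says.** The Sample size section of the protocol article names its endpoint: "Sample size is calculated based on the conversion event (number of clicks on the interaction with the antibiotic dashboard page, see Table 1". The comparison is between independent groups A, B and C. The variance comes from a usability test of a similar dashboard, which reported a "mean number of mouse clicks for dashboard usage (mean = 23.6 and standard deviation = 14.8". From these figures the section concludes: "A total sample size of 87 users or practices (29 per group) is estimated to be sufficient to observe a 10% difference", "with 5% statistical confidence". It gives no numerical power.

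The Participants section sets 1:1:1 randomisation at practice level. The Data analysis section fixes the test level: "All statistical tests will be 2-tailed and significance will be set at a p-value of 0,05".

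**The concern.** The SD is 63% of the mean (14.8 / 23.6). With that much spread, 29 observations per group cannot resolve a 10% difference in means. The section prints both its inputs and its result, so the claim can be checked directly, and the result does not follow.

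The sample-size statement tells a reader what a non-significant finding means. If 87 practices are believed sufficient for a 10% difference, a null result invites the conclusion that the key messages do not change clicks by as much as 10%. In fact a true 10% effect would be missed about nine times in ten. The opposite risk also exists: at the planned SD, a difference reaches significance only if it is observed at about 7.8 clicks or more. A significant result arising from a true difference of 2.36 clicks would then overstate it at least 3.3-fold (7.8 / 2.36).

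**Working it through.** **Inputs.** From Sample size: mean 23.6, SD σ = 14.8, difference 10%, n = 29 per group. From Data analysis: two-sided α = 0.05. Target power is not stated, so 50%, 80% and 90% are used below as benchmarks.

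**Effect.** δ = 0.10 × 23.6 = 2.36 clicks; d = δ/σ = 2.36 / 14.8 = 0.159.

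**Attempt to reproduce 29 per group.** The required number is n = 2σ²(z₀.₉₇₅ + z_power)² / δ².

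- 80% power: 2 × 219.04 × (1.960 + 0.842)² / 5.57 ≈ 618 per group (3 × 618 = 1,854 in total). The exact t calculation gives 618.3.
- 90% power: about 827 per group.
- 50% power: about 303 per group.

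None is near 29.

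**Power at 29 per group.** The standard error of a difference between two groups is 14.8 × √(2/29) = 3.89 clicks. The noncentrality is 2.36 / 3.89 = 0.61, against a critical value of t₀.₉₇₅,₅₆ = 2.00. Power is 9.2% (noncentral t), or 8.8% by normal approximation.

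**What 29 per group can do.**

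- Detectable difference at 80% power: 0.749 × 14.8 = 11.1 clicks (47% of 23.6).
- Detectable difference at 90% power: 0.866 × 14.8 = 12.8 clicks.
- 95% CI half-width for a difference between two groups: 2.00 × 3.89 = 7.8 clicks (33% of 23.6). This is also the smallest observed difference that reaches p = 0.05.
- For 2.36 clicks to be detectable with 80% power, the SD would have to be about 3.2 instead of 14.8.

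**Other readings of the claim, each with 29 per group.**

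| Reading | Power at 29 per group | n per group for 80% power |
|---|---|---|
| 10% of the mean, one-sided 5% | 15% | 487 |
| 10% of the mean, Bonferroni for three pairs (0.05/3) | 3.7% | 824 |
| Three-group ANOVA, largest gap 10% | 7.8–8.7% | 1,708–2,276 in total |
| Log-normal clicks, 10% ratio | 9.2% | 574 |
| Negative binomial, same mean and variance | 8.4% | about 677 |
| 10 percentage points, base rate 10–80% | 11–18% | 199–388 |
| 10 percentage points, base rate 5%, 85% or 90% | 24%, 24%, 41% | 141, 141, 74 |
| 10 clicks (42% of the mean), two-sided 5% | 72% | 36 |
| 10 clicks, one-sided 5% or two-sided 10% | 81.5% | 28 |

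Only the last row comes close to 29. It needs both a different unit from the one printed (clicks instead of percent) and a different test level from the one in Data analysis.

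**The case against.** The strongest points on the other side are these.

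- **A near match exists.** Ten clicks at one-sided 5% or two-sided 10%, with 80% power, needs 28 per group. A slip from 10 clicks to 10% is a plausible origin of the figure. This may explain the number but does not rescue the text, which says 10% and two-tailed 0.05. If that was the intention, the section still has to be corrected.
- **No power is stated.** The plan claims only "sufficient to observe a 10% difference", so strictly no power figure is contradicted, and 80% is the reviewer's benchmark. That stands, but it changes little: even 50% power needs about 303 per group. Read as a precision claim it fails too, because the interval is ±33% of the mean.
- **The SD may not apply.** It comes from a usability test elsewhere, whereas the endpoint is one month of use by a practice. The trial's real detectable difference may therefore be larger or smaller than 47% of the mean. This is fair, but 14.8 is the figure on which the plan rests its claim.
- **87 is not a cap.** Under Recruitment and Data collection, registration is open and every registering practice is randomised, so enrolment could exceed 87. The claim that 87 suffices remains unsupported.
- **The aim is exploratory**, and no decision rule is attached to a null result. This limits the harm, but a reader would still rely on the stated detectable difference.
- **The confidence wording is editorial**, since Data analysis gives the significance level correctly. Agreed.

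**Conclusion.** The concern holds. On the plan's own mean, SD, group size and two-sided 5% level, power for a 10% difference in clicks is 9.2%, and about 21 times as many practices (618 / 29) would be needed for 80% power. With 29 per group, 80% power is reached only at about 11.1 clicks, 47% of the mean.

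These figures assume that 10% is relative to the mean of 23.6, that the SD is 14.8 in each group, and that two groups are compared without adjustment for multiplicity. The 80% target is a convention, not a figure from the plan. Adjusting for three pairwise comparisons, or practices that register but never use the dashboard, would lower the power further. No reading consistent with the printed 10% and the two-sided 5% level yields 29 per group.

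**What to change.** Rewrite the Sample size paragraph so that difference, unit, significance level, power and n agree. Suggested text:

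> With 29 practices per group, an SD of 14.8 clicks and a two-sided 5% significance level, an unadjusted comparison of two groups has 80% power for a difference of 11 clicks (47% of the mean of 23.6). The 95% confidence interval for such a difference has a half-width of about 8 clicks.

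Delete the 10% claim and replace the phrase "with 5% statistical confidence" with the significance level. If 10 clicks was intended, say so and give the power that follows: 72% at two-sided 5%. If 87 is a feasibility number, say that too. Add that group differences will be reported as estimates with 95% confidence intervals, and that a non-significant result will not be taken as absence of a 10% effect.

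The cost is one paragraph and a less favourable stated detectable difference. No further practices are needed. Keeping the 10% target with 80% power would instead require about 1,854 practices.
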